#### Protocol amendments summary

| State "none" if no amendments                         |                |            |                                                                                                                                                                                                                                                                |
|-------------------------------------------------------|----------------|------------|----------------------------------------------------------------------------------------------------------------------------------------------------------------------------------------------------------------------------------------------------------------|
|                                                       | Version number | Date       | Provide reason for the amendment                                                                                                                                                                                                                               |
|                                                       |                |            | State which sections of the protocol were replaced, added or deleted                                                                                                                                                                                           |
| N/A - Response to REC comments                 | 1.1            | 27.06.2022 | Section 4.1.1. Update of inclusion criteria
Section 4.3.2. Update to withdrawal section                                                                                                                                                                     |
| Clarification of primary outcome and primary endpoint | 2.0            | 13.01.2023 | Cover page updated
Trial Summary: Including additional sites
Study design: Including additional sites
Section 3.2: Clarification to primary outcome
Section 3.3: Clarification to first secondary outcome
Section 3.4: Updated study flow chart |

|                                                                                                                 |     |            |                                                                                                                                                                                                                                                                                                                                                                                                                                                                                                                                                                              |
|-----------------------------------------------------------------------------------------------------------------|-----|------------|------------------------------------------------------------------------------------------------------------------------------------------------------------------------------------------------------------------------------------------------------------------------------------------------------------------------------------------------------------------------------------------------------------------------------------------------------------------------------------------------------------------------------------------------------------------------------|
|                                                                                                                 |     |            | 
Section 4.1.1: Removal of size requirement for Grade 3 tumours and correction of typographical error – replaced > with <math>\geq</math>
 
Section 4.2: Clarification for approach process when waiting for test results to confirm eligibility including introduction of approach email
 
Section 4.3: Clarification of postal consent process
 
Section 5.1: Clarification of process when both follow questionnaires due on the same day
 
Update to table of data collection
 
Appendix A – Updated to replicate end point definition
 |
| Clarification eligibility of patients receiving bridging therapy and on ordering samples for these participants | 2.1 | 24.03.2023 | 
Section 3.1: Clarification on process when a participant has received bridging therapy prior to surgery
 
Section 3.2: Clarification of primary outcome when endocrine treatment has been received
 
Section 4.1.2: Clarification on exclusion criterion 'Planned for neoadjuvant systemic therapy'
 
Section 5.2: Clarification that it is the first post-operative appointment date used for the post-operative follow-up questionnaire.
                                                                                                             |
| Rewording to primary outcome and correction to archiving section.                                               | 2.2 | 04.07.2023 | 
Section 3.2: Rewording to the primary outcome to ensure touchpoints from diagnosis to the offer of adjuvant treatment in captured.
 
Section 3.3: Additional secondary outcome of time between diagnosis and start of adjuvant treatment added
 
Section 10: 'and duration' removed from section as not possible as not being collected.
 
Section 16: Archiving corrected to 5 years from 10 years to reflect the IRAS form and PIS.
                                                                                                                  |

## ABBREVIATIONS

|         |                                                        |
|---------|--------------------------------------------------------|
| APR     | Annual Progress Report                                 |
| CI      | Chief Investigator                                     |
| CRF     | Case Report Form                                       |
| CTIMP   | Clinical Trial of an Investigational Medicinal Product |
| EDC     | Electronic Data Capture                                |
| ER+     | Oestrogen Receptor Positive                            |
| FNA     | Fine Needle Aspiration                                 |
| GCP     | Good Clinical Practice                                 |
| GP      | General Practitioner                                   |
| GDPR    | General Data Protection Regulation                     |
| HADS    | Hospital Anxiety Depression Score                      |
| HHTU    | Hull Health Trials Unit                                |
| HRUQ    | Health Resource Utilisation Questionnaire              |
| ICF     | Informed Consent Form                                  |
| ISF     | Investigator Site File                                 |
| MDT     | Multi-disciplinary Team                                |
| NHS R&D | National Health Service Research & Development         |
| NRES    | National Research Ethics Service                       |
| R&D     | Research & Development                                 |
| PI      | Principal Investigator                                 |
| PIS     | Participant Information Sheet                          |
| PPE     | Personal Protective Equipment                          |
| RCC     | REDCap Cloud (Electronic Database)                     |
| RCT     | Randomised Control Trial                               |
| REC     | Research Ethics Committee                              |
| RGF     | Research Governance Framework                          |
| RS      | Recurrence Score                                       |
| SDV     | Source Data Verification                               |
| SOP     | Standard Operating Procedure                           |
| TMF     | Trial Master File                                      |
| TMG     | Trial Management Group                                 |
| TSC     | Trial Steering Committee                               |
| UoH     | University of Hull                                     |

## TRIAL SUMMARY

The Oncotype DX® test is a prognostic and predictive genomic assay, validated and approved for use in early Oestrogen receptor positive (ER+) breast cancer to guide adjuvant systemic treatment. The Oncotype DX® test is performed following surgical treatment of breast cancer to more accurately determine patients who benefit from additional chemotherapy treatment. This multi-centre prospective randomised controlled trial (RCT) aims to ascertain the impact on the patient management pathway of performing the Oncotype DX Breast Recurrence Score® test on the pre-operative diagnostic core biopsy (intervention), as opposed to requesting the test on the post-operative excision specimen as it is in the current usual patient pathway. The study will analyse the effectiveness of the intervention arm pathway, as measured in patient touch points and the time from diagnosis to being offered adjuvant cancer therapy. The study will also explore if there is any alteration in the sequencing of treatments (e.g. use of neo-adjuvant strategies) in the intervention arm.

The study will recruit 330 participants from up to 25 sites across the UK.

## 1.0 BACKGROUND

Oncotype DX® is a prognostic and predictive genomic assay validated and approved by NICE for the use in early Oestrogen receptor positive (ER+) breast cancer to guide adjuvant systemic treatment [1]. The Recurrence Score® (RS®) result guides recommendations made to the patient regarding the requirement for adjuvant chemotherapy in addition to adjuvant endocrine therapy [2]. The Oncotype DX® test is currently performed on the operative specimen following surgical treatment of the breast cancer. This test more accurately determines the group of patients who benefit from the addition of chemotherapy. Using this test approximately 3/10 patients are shown to require chemotherapy.

It has been shown to be both technically possible and accurate to perform the Oncotype DX® test on the diagnostic core biopsy of the breast cancer prior to the surgical tumour excision procedure [3, 4], improving the timeliness of starting adjuvant treatment [5, 8]. Having the information provided by the Recurrence Score® results in the pre-operative setting would therefore be advantageous to the treating clinician and the patient. The treating clinician would be able to more accurately counsel the patient with regards to their treatment pathway and account for this in planning the patient's care. This would not only empower the patient with regards to the expectations of upcoming treatments but also expedite those treatments by eliminating the inherent delay in waiting for the RS results on the surgical excision specimen. In addition, the pre-operative knowledge regarding the type of oncological input required in the adjuvant setting will also allow the streaming of follow up appointments and mitigate against unnecessary and costly outpatient attendances.

## 2.0 AIMS AND OBJECTIVES

This study aims to compare the standard patient pathway (control arm), where the Oncotype DX® test is requested on the post-operative specimen with requesting the test on the pre-operative diagnostic core biopsy (intervention arm). The initial planned analyses will add to the evidence base of the patient management pathway of performing the Oncotype DX® test on the pre-operative diagnostic biopsy.

**Aim:** To assess the impact on patient management by the availability of the RS® results from the core biopsy in the pre-operative setting.

**Primary hypothesis:** The availability of the RS® results from the core biopsy in the pre-operative setting streamlines the patient management pathway

**Secondary hypothesis:** The availability of the RS® results from the core biopsy in the pre-operative setting reduces healthcare utilisation, improves patient experience and decreases the time to the offering of adjuvant cancer therapy.

## 3.0 STUDY DESIGN

A multi-centre, prospective parallel group randomised controlled trial with unequal random allocation (2:1; Intervention:Control) comparing the impact on the patient management pathway of performing the Oncotype DX® test on the diagnostic core biopsy in the pre-operative setting (intervention) as opposed to the surgical excision biopsy (control)#. The primary outcome and end point will be number of touchpoints between the treating team and the participant from the initial patient approach to the start of adjuvant cancer treatment. The study will recruit 330 participants from up to 25 sites across the UK.

### 3.1 INTERVENTIONS

For participants in the Standard arm, standard practice will be followed at each site for ordering and acting on the Recurrence Score® (RS®) result. The Oncotype DX® test is performed on excision samples obtained during surgery#.

#Participants receiving endocrine bridging therapy are eligible for the study provided the reason is that there has been a delay in planned surgery. Patients prescribed neo-adjuvant endocrine or chemotherapy for the purpose of downstaging are **not** permitted. In the event of the participant having received endocrine bridging therapy prior to surgery, as per routine practice, the use of the core biopsy for testing is permitted in the standard arm provided it is still ordered in the post-operative setting.

For participants in the Intervention arm, the Oncotype DX® test will be performed on the core biopsy that was taken at the time of diagnosis and the results of the Oncotype DX® test will be available to be discussed at the post-operative MDT meeting. The discussion will support decision-making on treatment options.

A failure of RS scores on the diagnostic biopsy sample would mean the test result being unavailable to support adjuvant treatment decisions for participants in the Intervention Arm. In the event of a failure on the diagnostic biopsy sample, the excision sample will be retested as per the surgical excision biopsy group. They will continue in the study in their original allocated group, being included in the primary intention to treat analysis.

Planned surgery will not be delayed if RS® results are unavailable and any change to the treatment recommendation will be recorded and discussed with the participant at an additional routine clinic appointment if required. If there is no change to the treatment recommendation, it will be left to the Centre's discretion whether to discuss the results with the patient before surgery but intentions of the centre will be recorded. If the event the decision is made to change the treatment pathway with the patient subsequently receiving neo-adjuvant or endocrine therapy prior to surgery, the clinical touchpoints, HADS and HRUQ would no longer be collected but the participants would be followed up until completion of treatment for final post-operative pathology.

In both arms of the study, the interpretation of the RS® result and treatment recommendations will be at the discretion of the MDT and treating clinicians following national guidelines.

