### **3.3. SECONDARY OUTCOMES**

- Time in days between the participant diagnosis (defined as the date of attendance at diagnostic clinic) and the offer and prescription of the first adjuvant cancer treatment (chemotherapy, radiotherapy or endocrine therapy)
- Time in days between the participant diagnosis (defined as the date of attendance at diagnostic clinic) and the start of the first adjuvant cancer treatment (chemotherapy, radiotherapy or endocrine therapy)

- Alteration in recommended treatment sequence. This would be defined as a when a participant in the intervention arm, as a result of the RS results from the core biopsy, receives neo-adjuvant treatment rather than proceeding directly to surgery. The clinical touchpoints, HADS and HRUQ would no longer be collected but the participants would be followed up until completion of treatment for final post-operative pathology.
- Participant reported anxiety score HADS score at the post-operative result clinic and following the offer of adjuvant treatment
- Health system cost impact analysis comparison of the intervention arm with the control arm
- Correlation of preoperative staging with postoperative pathological staging
- Rate of failure of the Oncotype DX® assay (RS result cannot be issued) on diagnostic core biopsy specimen

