#### **4.3.2 WITHDRAWAL OF PARTICIPANTS**

Participants remain free to withdraw at any time from the study without giving reasons and without prejudicing their further treatment. During discussions around the participants withdrawal, they should be provided the option of withdrawing fully or just from the study questionnaires (e.g. no further contact with study team but touch points still recorded).

If the participant is willing to provide a reason for the withdrawal, this should be recorded when completing the withdrawal on the study database, although the participants' right not to give a reason must be respected throughout. Data collected up

to the point of participant withdrawal will be included in data analysis but no further contact will be made with the participant.

The informed consent form includes a statement on the use of data after a participant withdraws from the study.

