### **11.2 STATISTICAL ANALYSIS:**

The reporting guideline of CONSORT 2010 statement [7] will be followed for analysis and reporting of this study. All statistical tests and confidence intervals will be two-sided.

Ninety-five percent confidence intervals will be presented with the significance of p value at 5% significance level. Analyses will be conducted on an intention-to-treat basis (all participants who are randomized are included in the statistical analysis, including those who fail to receive an RS result from either the diagnostic core biopsy or excision specimen) and follow a pre-specified statistical analysis plan. Baseline patient characteristics will be tabulated through descriptive statistics. For the primary outcome, comparison of the numbers of participant-clinician touch points will be undertaken using a Negative Binomial model, adjusting for stratification factors and other prognostic baseline covariates. Rate of alteration in treatment pathway and rate of failure of obtaining an RS result on diagnostic core biopsy specimen in the intervention arm will be summarised and a per-protocol analysis will be conducted as secondary analysis, excluding those with alteration in treatment pathway or failure to obtain RS result. Comparison of time between diagnosis and adjuvant treatment will be assessed via Cox regression controlling for the same stratification factors and prognostic covariates. HADS score at baseline, the post-operative result clinic and commencement of adjuvant treatment will be examined by linear regression controlling for the same stratification factors and prognostic covariates. Correlation of preoperative staging with postoperative pathological staging will be calculated.

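### Touchpoint recording stops after a switch to pre-surgical therapy, so the primary outcome is unobtainable for participants whom the intention-to-treat analysis must include, and the RS-driven switch arises in the intervention arm only

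*Protocol*

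**What the plan says.** **Outcome.** Protocol Section 3.2 counts participant–clinician contacts from diagnosis to the offer and prescription of the first adjuvant treatment. It has a special closing date for bridging therapy but none for a participant switched to neo-adjuvant treatment.

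**Stop rule.** Section 3.1 states that after a change to neo-adjuvant or endocrine therapy before surgery "the clinical touchpoints, HADS and HRUQ would no longer be collected but the participants would be followed up until completion of treatment", the purpose of that follow-up being final pathology. Section 3.3 repeats it: "The clinical touchpoints, HADS and HRUQ would no longer be collected".

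**Who is affected.** Section 3.3 describes the alteration as occurring "when a participant in the intervention arm, as a result of the RS results from the core biopsy, receives neo-adjuvant treatment" and so does not have the operation first. For standard-arm participants who have had bridging therapy, Section 3.1 says "the use of the core biopsy for testing is permitted in the standard arm provided it is still ordered in the post-operative setting".

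**Analysis set.** Section 11.2 promises intention to treat: "all participants who are randomized are included in the statistical analysis, including those who fail to receive an RS result". Altered pathways are a reason for exclusion only from the secondary per-protocol analysis.

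**The concern.** The per-protocol exclusion makes sense only if switched participants belong to the primary set. Yet sites are told to stop recording the primary outcome for exactly these people, before the window in Section 3.2 has closed. No section says what count they contribute. Participants with a failed RS are expressly kept in, and bridging therapy has its own endpoint, so this group is the gap.

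The loss depends on allocation. It follows from having the RS before surgery, which is what is randomised. The standard-arm participants who would have switched on the same RS stay in with complete counts.

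An unfinished running total is a low total, and a low total is what the trial would report as a streamlined pathway. A statistical analysis plan can choose how to treat missing counts, but it cannot recover counts that sites were told not to collect. The cost comparison in Section 10 draws on touchpoints and HRUQ, and both stop.

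**Working it through.** **Inputs from the protocol.** Control mean 6 and intervention mean 5 touchpoints; 2:1 allocation; 5% significance; 90% power; 20% dropout (Section 11.1). Two-sided tests (Section 11.2). Dispersion 0, with 88 and 176 evaluable (Appendix B).

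**Reproducing the plan's sample size.** The negative binomial rate-ratio formula with dispersion 0 is n₀ = (1.960·√V₀ + 1.282·√V₁)² / [ln(5/6)]².
- V₁ = 1/6 + 1/(2×5) = 0.2667.
- Pooled rate (6 + 2×5)/3 = 5.333, so V₀ = 1.5/5.333 = 0.2813.
- n₀ = (1.960×0.5303 + 1.282×0.5164)² / 0.03324 = 87.1, which rounds up to 88, with 2×88 = 176.
- 88/0.8 = 110 and 176/0.8 = 220, total 330. The plan's figure is reproduced.

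**Assumptions.** The protocol gives no switch rate p and no count c at the switch. I take p from 2% to 10% (about 4 to 22 of the 220 in the intervention arm) and c = 2, with c = 1 and 3 as a range.

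**Partial counts used as if complete, no true effect.** Ratio = [6(1 − p) + c·p]/6. Test: z = ln(ratio)/√(1/S₀ + 1/S₁), where S₀ = 88×6 = 528 and S₁ = 176 × the intervention mean.

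| p (c = 2) | Intervention mean | Ratio | S₁ | SE | Expected z | Two-sided rejection |
|---|---|---|---|---|---|---|
| 2% | 5.92 | 0.987 | 1,042 | 0.0534 | −0.25 | about 6% |
| 5% | 5.80 | 0.967 | 1,021 | 0.0536 | −0.63 | about 10% |
| 10% | 5.60 | 0.933 | 986 | 0.0539 | −1.28 | about 25% |

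Simulation of the same test agrees: rejection is about 5% with no switchers, and about 6%, 10% and 24–26% at 2%, 5% and 10%. With c between 1 and 3, 5% switchers give ratios of 0.96–0.98 and rejection of 8–14%; 10% give 0.92–0.95 and 17–37%. The planned ratio is 5/6 = 0.833.

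**Switchers dropped, no true effect.** If switchers would have averaged h touchpoints, those remaining average (6 − h·p)/(1 − p). With an assumed h = 8:
- p = 10%: (6 − 0.8)/0.9 = 5.78. The chance of a significant result favouring the intervention is about 10%, against 2.5% without bias.
- p = 20%: (6 − 1.6)/0.8 = 5.50, and about 34%.

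With h = 6 there is no such bias. Power hardly moves: by the Wald formula it is 0.912 with 176 analysed in the intervention arm and 0.900 with 158 (10% dropped). The problem is bias, and the 20% dropout allowance does not address it.

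**Counting switchers through to the post-operative offer.** With the planned effect, the ratio is [5(1 − p) + L·p]/6, where L is a switcher's full count. L is not in the protocol; assume 12 to 20. At p = 5%: (4.75 + 0.60)/6 = 0.89 to (4.75 + 1.00)/6 = 0.96. At p = 10%: (4.5 + 1.2)/6 = 0.95 to (4.5 + 2.0)/6 = 1.08.

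**The case against.** **Frequency.** Surgery must be planned as first treatment, planned neo-adjuvant therapy is excluded, and surgery is not held up for the RS. Switches may be rare, and at 2% the inflation is slight. This stands: the size is unknown. But the Trial Summary names altered sequencing as something to explore, so the event is foreseen.

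**Obvious remedy.** Counting to the post-operative adjuvant offer brings in contacts during neo-adjuvant treatment. A control participant given systemic treatment after surgery stops counting at its prescription. This stands. It shifts the estimate and does not merely add variance, so the choice of endpoint has to be explicit.

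**Stronger readings.** A reader might infer four things that the protocol does not support.
- *No primary analysis can be run.* A model can be fitted to partial or imputed counts. What cannot be had is the Section 3.2 outcome for all randomised participants.
- *The stop rule applies to one arm by its terms.* The Section 3.1 sentence names no arm, so a control participant switched for another reason could fall under it. Only the RS-driven switch is confined to the intervention arm.
- *Switchers are lost from the time-to-offer analysis.* The rule lists touchpoints, HADS and HRUQ. Treatment dates are not listed, and follow-up continues to completion of treatment.
- *Withdrawals are analysed as finished counts.* Section 4.3.2 says that data up "to the point of participant withdrawal will be included in data analysis but no further contact will be made". That is a data-retention statement. The same section lets participants leave only the questionnaires while touchpoints are still recorded, and handling incomplete counts after full withdrawal belongs in the analysis plan.

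**Conclusion.** The point holds. Sections 3.1 and 3.3 conflict with Section 11.2 on the primary outcome, and the RS-driven loss falls on the intervention arm. Using partial counts favours the intervention. Dropping switchers abandons intention to treat, and favours the intervention if they would have had more touchpoints than average.

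The size depends on a switch rate and a count at switch that the protocol does not give. Under the assumptions shown, it runs from negligible at 2% to a false-positive rate of about one in four at 10% with a cut at 2. Because the missing data arise from an instruction to sites, the instruction itself has to change.

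**What to change.** Amend Sections 3.1 and 3.3 to remove the stop rule for hospital-recorded touchpoints. For any participant in either arm whose sequence changes, record touchpoints with dates through to the first post-operative adjuvant offer and prescription.

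Reconcile Section 11.2 with this. Include all switchers in the intention-to-treat analysis and pre-specify which endpoint closes their count:
- the first systemic anti-cancer prescription; or
- the post-operative adjuvant offer, stated as a treatment-policy estimand.

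Report the other as a sensitivity analysis. Dated records allow both from one data collection.

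**Cost.** A protocol amendment and some extra entry from hospital records. No visits are added, since these participants are already followed to final pathology and the primary-outcome contacts in Appendix A are hospital-reported.

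**Downside.** Under the post-operative endpoint, RS-driven neo-adjuvant visits count in the intervention arm only and can move the ratio towards or above 1, so both results must be shown. HADS and HRUQ would still be missing for switchers unless those stops are also lifted, and the cost report should say so.
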